### Participants

#### Inclusion criteria

The inclusion criteria include the following: stage I or II hypertension with low to medium risk, which is diagnosed according to the Chinese Hypertension Guidelines published in 2018 [46]; the BP was continuously or more than 3 times in a non-same day sitting position with systolic BP ≥ 140 mmHg and < 180 mmHg and (or) diastolic BP ≥ 90 mmHg and < 110 mmHg; TCM syndrome is associated with kidney deficiency syndrome (TCM kidney deficiency syndrome is shown in Additional file 2); male or female; without taking any hypotensive drugs; aged between 18 and 75 years; the participants are volunteers, understand the process of this trial, and sign an informed consent.

#### Exclusion criteria

The exclusion criteria include the following: uncooperative patient; secondary hypertension (symptomatic hypertension); severe hypertension systolic BP ≥ 180 mmHg and/or diastolic BP ≥ 110 mmHg; severe heart failure; insulin-dependent diabetes; infectious diseases; hyperthyroidism, combined with severe primary diseases including liver, kidney, hematopoietic system, nervous system, mental illness, and malignant tumors; patients participating in other clinical trials; pregnant or breastfeeding women; and with recent history of trauma.

#### Withdraw criteria

The following are the withdraw criteria:
Those who are unwilling to continue clinical trials during the research periodThose who did not follow the prescribed protocol during the study periodThose who have not completed the course of treatment or have incomplete informationDuring the study period, those who applied drugs other than those specified in the study plan that affect the efficacy of observation

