### Endpoint measurements

#### Primary outcome

The primary outcome is the change in 24-h average systolic and diastolic BP, 24-h coefficient of BP variability (CV), morning BP, 24-h BP trough/peak ratio (T/P), 24-h BP smoothing index (SI) [49].

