### Data collection and management

The case report form (CRF) will be used for recording the process for each participant. In addition to the enrollment evaluation (− 7 ± 0 days), each participant will attend an evaluation visit when allocated and every 2 weeks afterwards during the trial (0 days, 2 weeks, 4 weeks, 6 weeks, and 8 weeks). The assessments including physical examination, improvement in symptoms, compliance with medications, questions about adverse events will be given to each participant. Blood tests and 24-h BP monitoring will be evaluated only at the enrollment and close-out visits. The schedule of enrollment, interventions, and assessments can be checked in Table 2. All researchers involved in data entry and data management will sign a confidentiality agreement to prevent data leakage. The personal information of all participants will be carefully protected, and the original CRF will be kept for 5 years after the end of the trial.

**Table 2 Tab2:** Schedule of the data collection

Process/item	Run-in period	Run-in period	Pre-treatment	Treatment period			
Time point	− 7 day	− 1 day	0 days	2 weeks	4 weeks	6 weeks	8 weeks

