### Statistical analysis

#### Sample size calculation

The formula used to calculate the sample size is as follows, which is based on superiority clinical trial interval hypothesis test sample size estimation [52]. The sample size was calculated based on the expected reduction in reducing of BP. One previous study suggested that the reduction of BP after interventional treatment is 4.5 mmHg, and the BP SD is 10 mmHg. Therefore, we assume the reduction of BP as 4.5 mmHg in this study. In the following formula, *c* is the ratio between two sample cases, *n*1 = *n*2, so *c* = 1. *σ* is the BP SD 10 mmHg, and *δ* is the expected effect BP 4.5 mmHg, so *σ* = 10 and *δ* = 4.5. Given a type I error rate of *α* = 0.05, a power of 90% (type II error rate of *β* = 0.1), so *uα* = 1.96, *uβ* = 1.282. *n1* = *n2* ≈ 104, the sample size for one group needs to be 104, resulting in *n* = 2 × 104 = 208 patients. Considering the maximum possible dropout rate is 20%, a total of 260 patients needs to be allocated to reach the required number of patients for the efficacy analysis.
$$ {\displaystyle \begin{array}{c}{n}_1={\left[\frac{\left( u\alpha + u\beta \right)\sigma }{\delta}\right]}^2\frac{\left(1+c\right)}{c},{n}_2=c{n}_1\\ {}{n}_1={n}_2\approx 104\end{array}} $$

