#### Planned data analysis

The intention-to-treat principle will be used to analyze the efficacy and safety of BSJY. The independent data administrator and the professional statistician will undertake data entry and data management, and perform the data analysis, respectively. All the efficacy and safety analyses with all randomly assigned participants included will be conducted within the full analysis set (FAS). The per-protocol set (PPS) analysis will also be conducted to compare the results from FAS and PPS. Demographic and laboratory characteristics will be calculated at baseline and after the treatment period for all patients. The statistical analysis will be done at Guang’anmen Hospital, China Academy of Chinese Medical Sciences in Beijing.

For continuous variables with normal distribution, the comparability of the characteristics between the two study groups will be assessed by using the *t*-test. While for the comparison of data with non-normal distribution, the non-parametric Mann-Whitney-Wilcoxon test will be used. Continuous variables will be expressed by mean ± SD. We will assess the paired *t*-test to compare the difference of the outcome between preintervention and postintervention in each group by using the independent *t*-test. A *χ*^2^ test will be used for categorical variables, while the Fisher exact test will be used when the theoretical frequency is less than 5 in more than 25% of the cells. Categorical variables will be shown as counts and percentages. Whether the hypothesis of superiority is available will be judged by comparing the 95%CI of the difference in intergroup efficacy. All statistical tests are unilateral tests; *p* < 0.05 is statistically significant. All statistical analyses will be performed using SPSS V.20.0.

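### Withdrawal criteria based on events after randomisation can cost participants their only post-baseline 24-h BP reading, which conflicts with the promised analysis of all randomised participants

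*Protocol article*

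**What the plan says.** Four statements in the protocol article bear on this point.

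- **Withdraw criteria.** Besides participants who no longer wish to take part, the list covers those who depart from the protocol, those who "have not completed the course of treatment or have incomplete" information, and "those who applied drugs other than those specified in the study plan that affect the efficacy of observation".
- **Planned data analysis.** "The intention-to-treat principle will be used to analyze the efficacy and safety of BSJY". The population is fixed as everyone randomised: "All the efficacy and safety analyses with all randomly assigned participants included will be conducted within the full analysis set (FAS"). A second set is announced beside it: "The per-protocol set (PPS) analysis will also be conducted to compare the results from FAS and PPS".
- **Primary outcome and its timing.** "The primary outcome is the change in 24-h average systolic and diastolic BP", listed with other BP measures. Under Data collection and management, "Blood tests and 24-h BP monitoring will be evaluated only at the enrollment and close-out visits". Table 2 shows one baseline 24-h reading and one at week 8. Visit BP is taken every two weeks, but it is not the 24-h average.
- **Sample size calculation.** The maximum dropout is put at 20%, and "a total of 260 patients needs to be allocated to reach the required number of patients for the efficacy analysis".

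**The concern.** Non-adherence, early stopping and use of other drugs are the usual reasons for leaving a per-protocol set. Here they are headed as reasons for withdrawal, and the Ethics section uses that word for leaving the trial. If they are applied that way before week 8, the participant leaves before the only post-baseline primary reading is taken. The analysis section nevertheless counts that participant among those to be analysed.

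All of these events occur after randomisation, and some are plausibly tied to the outcome. A participant whose BP stays high is a natural candidate for another antihypertensive drug or for stopping early. If that happens more often in the control arm, the control arm loses its poorer responders and the difference shrinks. If it happens more often in the BSJY arm, the difference is flattered. Either way, the comparison of those who remain no longer has the protection of randomisation, and recruiting more participants would not restore it.

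**Working it through.** **1. The plan's own figure.** Inputs from Sample size calculation: difference 4.5 mmHg, SD 10 mmHg, normal quantiles 1.96 and 1.282, equal arms.

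n per arm = 2 × [(1.96 + 1.282) × 10 / 4.5]² = 103.8, so 104 per arm and 208 in total. Allowing for 20% dropout: 208 / (1 − 0.20) = 260. The stated 104, 208 and 260 reproduce.

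**2. How many primary values could be missing.** 260 × 0.20 = 52. This is an upper figure: 20% is the protocol's stated maximum, and some of those who meet a withdrawal criterion may still attend week 8.

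**3. What the sections give when read together.**

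| Section | Consequence for a participant who takes another BP-lowering drug at week 4 |
|---|---|
| Withdraw criteria | Meets a criterion for withdrawal |
| Data collection and management; Table 2 | Has a baseline 24-h BP; the next is due at week 8 |
| Planned data analysis | Belongs to the FAS and is to be analysed |

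If withdrawal ends follow-up, the third row cannot be met from an observed primary value. The article does not say whether follow-up ends.

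**4. Illustration of possible size.** The documents give no removal rates by arm and no link between removal and response, so everything in this step is assumed. Take 130 per arm, normally distributed changes with SD 10, a true difference of 4.5 mmHg, and removal of exactly the worst-responding fraction q in each arm. With z the upper-q normal quantile, φ the standard normal density and λ = φ(z) / (1 − q):

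- shift in the mean of those who remain = 10 × λ
- SD of those who remain = 10 × √(1 − zλ − λ²)

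| q | z | λ | Mean shift (mmHg) | Remaining SD (mmHg) |
|---|---|---|---|---|
| 15% | 1.036 | 0.274 | 2.74 | 8.0 |
| 10% | 1.282 | 0.195 | 1.95 | 8.4 |
| 5% | 1.645 | 0.109 | 1.09 | 9.0 |

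*Control 15%, BSJY 5%.* The net shift is 1.66 mmHg from unrounded values, leaving 4.5 − 1.66 = 2.84 mmHg. With 110.5 and 123.5 analysed, SE = √(8.0²/110.5 + 9.0²/123.5) = 1.11. Power = Φ(2.84/1.11 − 1.96), about 72%.

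*Control 10%, BSJY 5%.* The net shift is 1.95 − 1.09 = 0.86 mmHg, leaving 3.64 mmHg. With 117 and 123.5 analysed, SE = √(8.4²/117 + 9.0²/123.5) = 1.12. Power is about 90%, close to the planned level.

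Swapping the rates between arms reverses the sign: the difference is then inflated by the same 1.66 or 0.86 mmHg.

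**5. A second set of assumptions.** If a fraction d is removed in each arm and those removed differ from completers by g mmHg in their change, the bias in the completer difference is (difference in d) × g. For 25% versus 15% removed, g of 5 to 10 gives 0.5 to 1.0 mmHg. For 30% versus 10%, it gives 1.0 to 2.0 mmHg. With equal removal and equal g in both arms, it is zero.

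**The case against.** The strongest reply is that the loss is inferred. No sentence bars a withdrawn participant from week 8 or leaves that participant out of the analysis, and the analysis section says that all randomised participants are included. Several criteria look backwards: failure to complete and incomplete information are often known only near the end, so they may serve as labels for dropouts more than as triggers for removal. Someone who missed doses or took another drug could still attend the close-out visit.

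This stands as a limit on the claim. A reader might infer that the trial plans a completer analysis, and the documents do not say so. Nor does the step from 208 to 260 confirm it: that is an ordinary dropout allowance, compatible with an intention-to-treat plan that expects some missing values. A reader might also infer that the FAS and the per-protocol set would hold nearly the same people, but the article does not define membership of the per-protocol set.

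Two further objections are accepted. Power must not be computed with the SD held at 10 once the tail has been removed, because that overstates the loss; the figures above use the reduced SD. And the method for values that remain missing may properly be left to an SAP that is not shown.

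What the reply does not remove is the conflict over data collection. An SAP can choose a method for missing values, but it cannot recover a week-8 reading that was never taken.

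**Conclusion.** The point holds as a conflict between the withdrawal criteria and the analysis section, made consequential by the single post-baseline 24-h reading. Followed as written, the plan can lose the primary value for participants it promises to analyse, up to 52 of 260 at the stated maximum dropout.

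The direction and size of any bias cannot be derived from the documents. The illustrations run from about 0.5 to 2.0 mmHg against an assumed effect of 4.5 mmHg. They rest on removal rates that differ between arms and on removed participants who respond differently, neither of which the documents state. The power figures also take the 1.96 quantile from the sample size section.

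**What to change.** Reconcile Withdraw criteria with Planned data analysis:

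1. Distinguish departure from study treatment or from the protocol from leaving the study.
2. Record non-adherence, early stopping, incomplete information and use of other drugs as events that do not end outcome collection.
3. Obtain the already scheduled week-8 24-h BP from every participant who still consents, and analyse it in the assigned arm.
4. Use the present criteria only to define the per-protocol set.

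This concerns outcome collection and analysis sets, not who should stop or receive treatment.

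The cost is a change of wording and some effort to bring non-completers to a visit that is already scheduled. The estimate will include off-treatment data and may be slightly smaller. The change was feasible when the article was submitted: Trial status reports 80 participants recruited and followed up, recruitment continuing and no analysis done, which leaves 260 − 80 = 180 still to be enrolled.

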### Ethics

The protocol (version 4.0, dated 09 October 2019) was approved by the clinical research ethics committee of Guang’anmen Hospital of the China Academy of Chinese Medical Sciences (approval 2019-186-KY-01), where the study will take place. It has been registered with the Chinese Clinical Trial Registry (ChiMCTR1900002876), which is listed in the WHO Registry Network. The Declaration of Helsinki and the principles of Good Clinical Practice were complied with by this trial [47, 48]. The participants must sign an informed consent form before enrollment. Meanwhile, they have the right to withdraw from the trial at any time.

### Randomization and blinding

The generated random tables were developed with Statistical Analysis System (SAS, version 9.4) by randomization biostatisticians. All the participants were included in the clinical trial according to the order of random table numbers. The ratio of the two groups was 1:1. For blinding, 260 sealed opaque envelopes were used to keep the allocation code for each participant, which were not accessible to the researchers, participants, clinical trial pharmacists, data managers, or statisticians. The BSJY granule was similar to its placebo in each group. The manufacturer, Sichuan Neo-Green Pharmaceutical Technology Development Co., Ltd., labeled the random codes on the package according to the principles of GCP.

### Intervention

BSJY (production batch number 191201), the placebo for BSJY (production batch number 191201), were produced and packed in a single batch by Sichuan Neo-Green Pharmaceutical Technology Development Co., Ltd. (Unified Social Credit Identifier 91510000684559613P). As tested, the drug conformed with the quality specified in the Chinese medicine standards published by the State Food and Drug Administration. Each bag of BSJY granule was 14.91 g and made from 138 g of the original drug. The main component of the placebo for BSJY is dextrin and 10% original drug. The BSJY and placebo granules (one bag at a time, two times per day, 8 weeks) will be provided by Sichuan Neo-Green Pharmaceutical Technology Development Co., Ltd. (Peng Zhou, China). Amlodipine besylate tablets (one tablet at a time, once per day, 8 weeks) were bought from Pfizer Co., Ltd. (Unified Social Credit Identifier 912102006048147187).

### Endpoint measurements

#### Primary outcome

The primary outcome is the change in 24-h average systolic and diastolic BP, 24-h coefficient of BP variability (CV), morning BP, 24-h BP trough/peak ratio (T/P), 24-h BP smoothing index (SI) [49].

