**Methods and analysis:**

This trial is a one-center, randomized, double-blind, placebo-controlled study. A total of 260 participants will be randomized in a 1:1 ratio to an experimental group (BSJY plus amlodipine) and a control group (placebo plus amlodipine). The trial cycle will last 8 weeks. The primary outcome is the change in 24-h average systolic and diastolic blood pressure. The secondary outcomes include heart rate variability, pharmacogenomic evaluation, improvement in TCM syndrome, and serum pro-inflammatory/anti-inflammatory cytokines between the two groups. The safety of medication will also be evaluated. All the data will be recorded in electronic case report forms and analyzed by SPSS V.22.0.

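### The primary outcome is six measures in the body, two in the abstract and one unspecified BP in the sample size, with no statement of which decides superiority

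*Protocol article*

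**What the plan says.** - **Abstract, Methods and analysis:** "The primary outcome is the change in 24-h average systolic and diastolic blood pressure". Two measures, given as the whole primary outcome.
- **Endpoint measurements, Primary outcome:** the same two 24-h averages, and with them "24-h coefficient of BP variability (CV), morning BP, 24-h BP trough/peak ratio (T/P), 24-h BP smoothing index (SI"). Six measures, unranked. The four extra ones appear in neither list of secondary outcomes.
- **Sample size calculation:** from one previous study, "the reduction of BP after interventional treatment is 4.5 mmHg, and the BP SD is 10 mmHg"; then "Therefore, we assume the reduction of BP as 4.5 mmHg in this study". The text does not say systolic or diastolic, 24-h or clinic. It uses 1.96 for alpha and 1.282 for 90% power.
- **Planned data analysis:** all tests are one-sided at p < 0.05, and superiority is judged from the 95% confidence interval of the between-group difference in efficacy. The outcome to which that interval belongs is not named.

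**The concern.** A reader cannot tell from this document what result would make the trial positive. The abstract and the body disagree on which measures are primary, and the sample size is tied to neither list. A difference in mmHg cannot size a coefficient, a ratio or an index, so at least three of the six primary measures have no stated basis for power.

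The analysis section applies the same threshold to every test and names no deciding outcome. As written, superiority could be claimed on whichever primary measure favours the herbal granule. If instead all the named measures must succeed, the stated power was calculated for one comparison and not for the joint requirement. Either way, the type I error or the power of the primary claim is not what the plan appears to promise.

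**Working it through.** **Inputs from the documents.** Difference δ = 4.5 mmHg, SD σ = 10 mmHg, normal quantiles 1.96 and 1.282, dropout 20% (Sample size calculation). Allocation 1:1 (Randomization and blinding). One-sided p < 0.05 (Planned data analysis).

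**Assumptions, because the documents give no values.** Equal correlation ρ between test statistics, from 0 to 0.8. For joint power, 4.5 and 10 mmHg hold for both 24-h SBP and 24-h DBP.

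**Step 1. The plan's own figure.** n per arm = 2 × [(1.96 + 1.282) × 10 / 4.5]² = 103.8, rounded up to 104. Total 2 × 104 = 208, and 208 / 0.80 = 260. The stated figures reproduce, for a single comparison. At 104 per arm the expected test statistic is 4.5 / (10 × √(2/104)) = 3.245. Power for one outcome is Φ(3.245 − 1.96) = 90.1% at 1.96 and Φ(3.245 − 1.645) = 94.5% at one-sided 0.05.

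**Step 2. Which alpha.** The sample size's 1.96 corresponds to one-sided 0.025, but the analysis section says one-sided 0.05. The 95% interval, if two-sided, again corresponds to one-sided 0.025. The results are therefore shown at both levels and not mixed.

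**Step 3. If success on any one outcome counts.** With independent tests the family-wise error is 1 − (1 − α)^k:
- k = 6: 1 − 0.95⁶ = 26.5%; 1 − 0.975⁶ = 14.1%.
- k = 2: 1 − 0.95² = 9.75%; 1 − 0.975² = 4.9%.

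With equicorrelated normal statistics, the error is the probability that the largest exceeds the cut.

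| Outcomes | ρ | one-sided 0.05 | one-sided 0.025 |
|---|---|---|---|
| 6 | 0 | 26.5% | 14.1% |
| 6 | 0.5 | 18.6% | 10.4% |
| 6 | 0.8 | 12.6% | 6.9% |
| 2 (SBP, DBP) | 0 | 9.8% | 4.9% |
| 2 (SBP, DBP) | 0.8 | 7.5% | 3.9% |

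**Step 4. If SBP and DBP must both succeed.** There is no inflation of type I error; the cost is power. With independent statistics, joint power is the square of the single-outcome power: 0.901² = 81.1% at 1.96 and 0.945² = 89.3% at one-sided 0.05. From the bivariate normal with mean 3.245 in each component:

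| ρ | cut 1.96 | cut 1.645 |
|---|---|---|
| 0 | 81.1% | 89.3% |
| 0.7 | 84.8% | 91.2% |
| 0.8 | 85.7% | 91.8% |

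The shortfall against 90% is real at the quantile used to size the trial. At the one-sided 0.05 of the analysis section it is negligible or absent.

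**The case against.** **The analysis plan may hold a multiplicity procedure.** It is not shown, and a journal article need not reproduce a hierarchy or an alpha split. This stands: the lack of an adjustment procedure here is not the finding. It does not remove the point, because the identity of the primary outcome belongs in the protocol. An analysis plan that chose one list would contradict either the abstract or the body.

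**The inflation is conditional.** A reader might infer that the trial runs a 26.5% false-positive risk. The document does not support this. It never says that one success suffices, it gives no correlations, and all six measures come from BP recordings and may be well correlated. Counting ten tests, by doing four of the measures for both SBP and DBP, would also be an assumption.

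**Error and power must be read at the same alpha.** It is tempting to pair an SBP-or-DBP error of about 8% to 10% with a both-must-succeed power of 81% to 86%. The first belongs to one-sided 0.05 and the second to 1.96, so they cannot both describe this trial.

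**Change in T/P and SI.** A reader might argue that these have no baseline value, so that a change in them cannot be calculated. The document defines neither index; it cites a source that is not at hand. The phrase about change may also govern only the 24-h averages. The argument is not made here.

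**24-h SBP as the basis of the sample size.** This might be inferred, but the calculation says only BP. Co-primary SBP and DBP would resolve the conflict as well as a single measure would.

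**Conclusion.** The concern holds as a conflict over what is primary. The abstract, the Primary outcome section and the Sample size calculation give three different answers, and the analysis section applies an unadjusted p < 0.05 without naming the outcome that decides superiority. This should be fixed before any analysis, because it determines what the trial can conclude.

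The size depends on a rule that the document does not state. Under an any-one rule, six outcomes raise the error to between 2.5 and 5.3 times a nominal 5% (12.6/5 to 26.5/5), or between 2.8 and 5.6 times a nominal 2.5% (6.9/2.5 to 14.1/2.5). For SBP or DBP alone the factor is 1.5 to 2.0 at either level. Under a both-must-succeed rule, power falls short by about 4 to 9 percentage points at 1.96 and hardly at all at one-sided 0.05. All of this rests on assumed correlations of 0 to 0.8, and the power also on equal standardized effects for SBP and DBP.

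**What to change.** Before any analysis:

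1. Make the abstract, the Primary outcome section and the Sample size calculation agree. Restrict the primary outcome to 24-h mean BP, as in the abstract.
2. Preferably name one measure, for example the between-group difference in change in 24-h mean SBP from baseline to week 8, then test 24-h mean DBP in fixed sequence at the same alpha. This holds the family-wise error at that alpha. If 4.5 and 10 mmHg are confirmed for the named measure and 1.96 is kept, 260 patients still give 90% power for the first test. The alternative is to declare SBP and DBP co-primary, both required, and restate the power (81% to 86% at 1.96 under the assumptions above).
3. State which BP measure the 4.5 and 10 mmHg describe, and state the power at the alpha that the analysis will use.
4. Move CV, morning BP, T/P and SI to the secondary outcomes.

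The cost is a protocol and registry amendment, and four measures lose primary status. Data collection does not change. The Trial status section reports that recruitment continues and that no analysis has been conducted, so the choice can still be made without knowledge of results.
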